### Symptom measures

#### Irritability

Irritability symptoms will be measured using the parent- and youth-report versions of the Affective Reactivity Index (ARI, [67]). In addition to item-level responses to the six parent-report and six youth-report items, a total parent-report ARI and child-report ARI score will be calculated as the sum of the six items.

#### Anxiety

Anxiety symptoms will be measured using the parent- and youth-report versions of the Screen for Anxiety Related Emotional Disorders (SCARED; [68]). Subscale scores will be calculated for each of the five subscales (Generalized Anxiety, Panic, School Anxiety, Separation Anxiety, and Social Anxiety) separately for the parent- and youth-report SCARED. Total parent- and child-report SCARED Total scores will also be calculated as the sum across all items.

#### ADHD

ADHD symptoms will be measured using the parent-report Conners Comprehensive Behavior Ratings Scale (CBRS; [69]). ADHD symptoms will be measured using the DSM-IV ADHD Total raw score. Additionally, using results of a confirmatory factor analysis examining the factor loadings of each individual item from the DSM-IV ADHD Total Score loading on a single latent factor, we have selected the six items with the highest factor loadings (S1 File).

Secondary analyses will be conducted examining associations with the two components of ADHD: hyperactive-impulsivity and inattentiveness. For these analyses, the CBRS DSM-IV Hyperactive-Impulsive and CBRS DSM-IV Inattentive subscales will be used.

#### Depression

For secondary analyses, depression symptoms will be measured using the parent-report Mood and Feelings Questionnaire (MFQ; [70]). Total scores on the MFQ will be calculated for each participant as a measure of depressive symptoms.

### Bifactor model of symptoms

Latent factor scores for shared vs unique variance of irritability, anxiety, and ADHD symptoms will be estimated using confirmatory factor analyses of an extended bifactor model (Fig 3; [59,61]). A general factor will be estimated using the six parent-report ARI items, five parent-report SCARED subscale scores, and six CBRS items identified by the CFA analysis. An irritability-unique, anxiety-unique, and ADHD-unique factor will be estimated using the ARI items, SCARED subscale scores, and six CBRS items respectively. Consistent with past work, model fit will be assessed using the following criteria: Tucker Lewis Index (TLI) and Comparative Fit Index (CFI) values > .950, and a Root Mean-Square Error of Approximation (RMSEA) value < .08. Factor scores on each of the resulting four latent factors will be extracted for each participant.

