### *Aim 3*: Identify clinical correlates of mobile application-based behavioral metrics

Finally, our third aim is to identify clinical correlates of mobile application-based measures of inhibitory control. Specifically, we will examine associations between mobile application-based behavioral measures of inhibitory control with shared vs. unique variance of three symptoms present across a wide range of pediatric psychopathologies: ADHD, anxiety, and irritability symptoms.

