### *Aim 3*: Identify clinical correlates of mobile application-based behavioral metrics

First, raw bivariate correlations between raw total scores on the five symptom measurements and CALM-IT d’ will be examined. Next, associations with shared vs. unique variances of anxiety, irritability, and ADHD symptoms will be examined using multiple regression analyses. All four latent factor scores from the bifactor model will be entered as concurrent predictors of CALM-IT d’. For all models, any demographic variable that varies as a function of either symptoms and/or CALM-IT d’ will be included as a covariate (i.e., age, sex, and IQ). Finally, secondary analyses will be run examining bivariate correlations between measures of hyperactive-impulsivity, inattentiveness, and depression.

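### The fit criteria for the symptom bifactor model cannot show whether its general factor is shared across domains, so Aim 3 could report a one-domain effect under the shared label

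*Protocol article*

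**What the plan says.** Under 'Bifactor model of symptoms', the protocol article defines four factors on 17 indicators. The general factor draws on all three parent-report scales: "A general factor will be estimated using the six parent-report ARI items, five parent-report SCARED subscale scores, and six CBRS items identified by the CFA". For the other three factors the article says: "An irritability-unique, anxiety-unique, and ADHD-unique factor will be estimated using the ARI items, SCARED subscale scores, and six CBRS items respectively". The bar for the model, described as in line with past work, is that "model fit will be assessed using the following criteria: Tucker Lewis Index (TLI) and Comparative Fit Index (CFI) values > .950". The third limit concerns approximation error: "a Root Mean-Square Error of Approximation (RMSEA) value < .08". The step that comes after is: "Factor scores on each of the resulting four latent factors will be extracted for each participant".

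Aim 3 gives these scores their meaning. Its question is the association of d' with "shared vs. unique variance of three symptoms present across a wide range of pediatric psychopathologies". The analytic plan for that aim first examines raw correlations of symptom totals with d'. It then turns to the latent scores: "All four latent factor scores from the bifactor model will be entered as concurrent predictors of CALM-IT" (the outcome being d'). Between the fit criteria and the use of the scores, the article states no check on what the general factor represents.

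**The concern.** A global fit index compares the model-implied covariance matrix with the observed one. It is silent on which indicators define a factor. A bifactor model can fit very well when its general factor is carried evenly by three domains, and equally well when it is almost one domain with weak loadings from the other two. In the second case that domain's unique factor holds little.

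The shared-versus-unique distinction is the whole question of Aim 3. If irritability led the general factor and d' were related only to irritability, the regression would tend to show a significant general score and a non-significant irritability-unique score. Read by the labels, that is a transdiagnostic correlate, when the true correlate is one domain.

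**Working it through.** **Inputs from the article.** 6 ARI items + 5 SCARED subscales + 6 CBRS items = 17 indicators; one general and three specific factors; CFI and TLI > .950, RMSEA < .08; 200 youth. The article's one power figure for the full sample, r ≥ 0.20 (stated for Aim 1a), reproduces at 0.197 (two-sided 0.05, power 0.80). No stated number is disputed here.

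**Inputs assumed.** Loadings, domain correlations, continuous normal indicators, and d' related only to irritability with r of 0.30 in size.

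**Step 1: degrees of freedom.** 17 × 18 / 2 = 153 moments. Free parameters: 17 general loadings + 17 specific loadings + 17 residuals = 51. df = 153 − 51 = 102.

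**Step 2: algebra.** If general and specific loadings are proportional within each domain, r(irritability, anxiety) = gI·gA, r(irritability, ADHD) = gI·gD and r(anxiety, ADHD) = gA·gD. The general factor's share of irritability's common variance is then

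gI² = r(irritability, anxiety) × r(irritability, ADHD) / r(anxiety, ADHD).

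With correlations in the order irritability–anxiety, irritability–ADHD, anxiety–ADHD:

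- all 0.50: 0.50 × 0.50 / 0.50 = 0.50
- 0.40/0.50/0.30: 0.67
- 0.30/0.50/0.20: 0.75
- 0.35/0.50/0.15: 1.17, which is not an admissible share; no irritability-unique factor exists there

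When r(anxiety, ADHD) equals the product of the other two, the share is exactly 1. The model then reproduces the data perfectly with the general factor equal to irritability.

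**Step 3: simulation from assumed loadings.** Maximum-likelihood fit, regression factor scores, 300 samples of n = 200 per population. Share = g² / (g² + s²), where g and s are a domain's general and specific loadings; for example 0.78² / (0.78² + 0.15²) = 0.96. The last two columns give the percentage of samples with p < .05.

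| Population | General share, ARI/SCARED/CBRS | Meet all cut-offs | r of general score with ARI/SCARED/CBRS sums | General | Irritability-unique |
|---|---|---|---|---|---|
| Balanced | 0.45/0.50/0.45 | 100% | 0.74/0.75/0.74 | 40% | 52% |
| Irritability-led | 0.96/0.10/0.11 | 100% | 0.94/0.33/0.36 | 81% | 31% |
| Milder lead | 0.90/0.15/0.22 | 100% | 0.96/0.37/0.49 | 79% | 23% |
| General = irritability | 1.00/0.15/0.16 | 100% | 0.97/0.38/0.43 | 84% | 21% |

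At n = 500 every sample still met the cut-offs. In the three irritability-led populations the general score was significant in 95–97% and irritability-unique in 15–33%. The cut-offs do not separate the rows; the domain shares do.

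**Step 4: simulation from the assumed correlations of Step 2** (loadings about 0.65–0.80, n = 200; ranges over repeated sets of runs).

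- All cut-offs met: 99–100% of samples, balanced or skewed.
- General significant and irritability-unique not: 57–77% in the three skewed settings, 32–35% with all correlations 0.50.
- Raw correlations pointing to irritability: 93–100%.
- Three domain totals entered together, irritability alone identified: 83–87% in every setting.

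**Step 5: would a reliability cut-off help?** Take H = Σ[l²/(1−l²)] / (1 + Σ[l²/(1−l²)]) for a unique factor with specific loadings l. With all correlations 0.50 and the midpoint loading 0.725, l² = 0.5 × 0.725² = 0.263 and l²/(1−l²) = 0.263/0.737 = 0.357. Six indicators: 2.14/3.14 = 0.68. Five: 1.78/2.78 = 0.64. So requiring H ≥ 0.70 fails a perfectly balanced model. Combined with a limit of 80% on any domain's general share, such a rule was met in 2–4% of balanced samples and 6–17% of skewed ones, so it does not discriminate in the right direction.

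**The case against.** The case on the other side is substantial.

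- **Nothing stated is false.** These are fit criteria used to assess fit, tied to past work that is not shown. A reader might infer that the model is accepted on these three indices alone. The article does not say so; it only names no other criterion, and loading tables are often left to a fuller plan or the results. This limits the wording of the point. The point remains, because the article itself fixes both the numeric criteria and the shared/unique reading, and the first cannot support the second.
- **Dominance is assumed.** A reader might infer that the general factor will be almost entirely irritability. The documents give no loadings or domain correlations and do not support that. At a share of 0.67 the general score still correlated 0.65 with ADHD. The 0.35/0.50/0.15 setting has no irritability-unique factor to find, so a null result for that score would be correct there; only the shared label on the other score would mislead. The algebra of Step 2 also needs proportional loadings, which the planned model does not impose.
- **A partial safeguard exists.** The raw correlations come first and would nearly always point to irritability. This stands, and it reduces the harm. But they do not adjust for the other domains and do not change what the general score is called.
- **Part of the size is low power.** The misleading pattern appears in about a third of samples even with equal correlations. So the excess in the skewed settings, not the whole 57–77%, is attributable to one domain leading.

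Rating-scale items will also fit less perfectly than simulated normal ones, and the extended part of the model cannot be seen because its figure is not shown. Neither makes a global fit index sensitive to which domain leads.

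**Conclusion.** The point holds as a conditional one. The stated criteria cannot tell a general factor shared by three domains from one led by a single domain. Should one domain lead, an effect specific to it can appear in Aim 3 mainly under the shared score. Under the assumed skewed correlations this happened in 57–77% of samples, against 32–35% under equal ones, with d' related to irritability alone at 0.30 and n = 200; n = 500 did not remove it. The figures rest on assumed loadings and correlations. They do not predict what this sample will show, nor do they show the bifactor model to be the wrong choice. Because the raw correlations would expose the association, this is a cheap improvement rather than a fault that undermines the aim.

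**What to change.** Keep the bifactor model and its fit criteria, and add two things to the plan.

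1. From the same fit, report the share of each domain's common variance carried by the general factor and the reliability of each unique factor. Describe the general score as shared across domains only as far as those shares support it. Do not attach a hard cut-off such as H ≥ 0.70 or an 80% share, given Step 5.
2. Beside the bifactor regression, regress CALM-IT d' on the three parent-report domain scores (ARI, SCARED, CBRS ADHD) entered together with the same covariates. Base any claim about a single domain on that model. State that a non-significant unique factor will not be read as absence of a domain-specific effect.

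The cost is a few lines of text and one extra regression on data already collected. The downside is that the shared-variance claim may have to be narrowed.

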**Fig 3 pone.0252245.g003:**
[figure not shown]
Bifactor model for clinical symptoms. Note: ARI P = Parent-Report Affective Reactivity Index, SCARED P = Parent-Report Screen for Anxiety Related Emotional Disorders, CBRS = Conners Comprehensive Behavior Ratings.

## Analytic plan

### Aim 1: Assessment of feasibility and consistency of CALM-IT

#### CALM-IT adoption and completion

First, we will assess mobile application adoption by calculating the percentage of participants who agreed to play the mobile application out of those who were contacted to assess interest. Second, we will assess mobile application completion by calculating the percentage of levels with complete and usable data for each participant who agreed to play the app.

#### CALM-It engagement

Performance on the mobile application will be evaluated to assess whether participants understand the visual instructions and were engaged in the task. The percentage of targets hit and the percentage of stars hit will be assessed as measures of correct engagement and incorrect engagement in task behavior, respectively. Average percent targets hit and percent stars hit will be reported across all participants. Average percent targets hit and percent stars hit will also be examined across each level to assess maintenance of attention and engagement across all levels of the task. Finally, a follow-up interview will be conducted to collect a qualitative assessment of CALM-IT engagement from each participant.

#### Extracting mobile application-based measures of inhibitory control

Using SDT we will extract a measure of sensitivity, or the discrimination between noise and signal, as a measure of inhibitory control using mobile application behavior. The variable d-prime (d’) assesses the degree of overlap between the standardized probability of hit trials (i.e. Hit Rate) and the standardized probability of false-alarm trials (i.e. False Alarm Rate; Eq 1; [71,72]). A value of 0 represents an inability to discriminate signal from noise with increasing values representing being better able to discriminate signal from noise. Values for d’ will be calculated for each participant using the psycho package in *R* [73].

$$d^{\prime }=z(Hit\;Rate)-z(False\;Alarm\;Rate)$$
(1)

Using d’ we will assess both individual differences in inhibitory control and average discrimination on the task. An average d’ value will be assessed across all participants to whether, on average, participants are able to discriminate between noise and signal on the task. Both the average d’ value and the receiver operating characteristic (ROC) curve will be reported to provide a graphical visualization of how often false alarms versus hits occur at any level of sensitivity.

#### Stability of mobile application-based behaviors

In the subset of participants who completed the mobile application twice, one week apart from another, the temporal stability of mobile application behaviors will be assessed using test-retest reliability. Specifically, we will examine test-retest reliability through examination of correlation between time-one with time-two measures of percentage of targets hit, percentage of stars hit, and d’. Consistency will also be reported using the intraclass correlation coefficient (ICC). In contrast to the Pearson’s correlation coefficient, ICC captures not only the degree of correlation, but also the agreement across measurements [74,75]. Because we are investigating test-retest reliability, or the stability across measurement, we will use ICC(3,1) which is a two-way mixed effects assessment of consistency within a single measurement. An ICC value of less than 0.40 would indicate poor consistency, an ICC value of 0.40–0.70 would indicate moderate consistency, an ICC value of 0.70–0.90 would indicate good consistency, and an ICC value greater than 0.90 would indicate excellent consistency.

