There is a profound need for mental health treatment research efforts to probe underlying mechanisms to inform diagnosis and treatment decisions [1–4]. Clinical researchers are well poised to harness new technologies to increases access, enhance developmental approaches, and assess transdiagnostic behavioral mechanisms underlying psychopathology [53,54]. Efforts to translate this work to clinical settings is crucial as providing clinicians with tools to directly probe behavioral mechanisms could lead towards increased precision medicine, patient engagement, and cost-effectiveness [55–57]. However, application of these innovations in clinical settings is lagging [53,54]. Few clinical approaches attempt to directly probe the aberrant brain-based behavioral mechanisms that have been linked to psychopathology [58] while also providing practical use in clinical settings. A significant contributing factor is researchers’ inability to create neuroscience-informed paradigms that are easily disseminated, suitable and practical for clinical use.

The goal of the present work is to leverage the strong psychometric properties of a canonical inhibitory control task in the creation of CALM-IT. By targeting a precise pathophysiologically-informed mechanism, and using a platform that is highly engaging and easily disseminated in pediatric samples, the mobile application CALM-IT was designed to bridge the gap between precise mechanisms-driven basic science research and community-based assessment of childhood psychopathology. CALM-IT is designed to leverage the strong methodological design of well-established laboratory based inhibitory control tasks while increasing participant engagement through gamification of the tasks. By using a mobile platform, participant interaction with CALM-IT mirrors those with other mobile-based games with the goal of increasing participant engagement via dynamic stimuli and in-game incentives. The development of CALM-IT would allow clinicians and researchers to screen for and track inhibitory control deficits in the community. This could extend the investigation of inhibitory control beyond the confines of the laboratory setting, therefore facilitating access to a larger and more diverse sample of patients. Ultimately, CALM-IT could lead to novel clinical screening measures for inhibitory control deficits that could be used to inform a personalized course of treatment.

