To investigate the feasibility of CALM-IT (***Aim 1a***), we will recruit 200 youth. For investigation of the stability of CALM-IT (***Aim 1b***), we will invite 75 youth out of the overall sample of 200 to play CALM-IT twice. For validation of mobile application-based behaviors of inhibitory control (***Aim 2***), we will invite 100 youth out of the overall sample of 200 to complete a battery of in-laboratory inhibitory control paradigms. We evaluated each of these proposed sample sizes using the pwr package in R to determine the size of the effect that the sample would allow us to detect using a significance level of 0.05 and a power level of 0.80 [64]. For the feasibility of CALM-IT (***Aim 1a***), our proposed sample size is sufficient to detect effects of *r*≥0.20. For the stability of CALM-IT (***Aim 1b***), our proposed sample size is sufficient to detect effects of *r*≥0.32. Finally, for the validation of application-based behaviors of inhibitory control (***Aim 2***), the proposed sample size is sufficient to detect effects of *r*≥0.28. Thus all proposed samples would allow us sufficient power to detect small to medium effect sizes that are similar to those found within comparable samples [7,47,65,66].

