**Fig 1 pone.0252245.g001:**
[figure not shown]
Screenshots depicting gameplay during CALM-IT. (A) Tutorial screen with the instructions to swipe targets (red, purple, and blue objects) and avoid swiping stars (yellow) (B) Screen capture from in-level play depicting targets and stars (C) Explosion and negative point indicator feedback in response to incorrectly swiping a star (D) Display of end of level cumulative score.

CALM-IT is comprised of 10 separate galaxies (e.g. levels). Each galaxy includes 13 stars and 39 targets and takes approximately 1 minute long to complete for a total of approximately 10 minutes of gameplay. Gameplay in the first five galaxies was modeled after the Go/No-Go paradigm [29]; targets represent go-stimuli and stars represent no-go stimuli. The last five galaxies were modeled after the Stop Signal Delay paradigm [31] such that 25% of the targets (e.g. go-stimuli) turn into stars (e.g. no-go stimuli) a a random time within two seconds of appearing on the screen. If a participant hit the go-turned-no-go stimuli, they receive the same explosion feedback image and accompanying sound as one does when you hit a star. Unlike standard Stop Signal Delay paradigms, for the go-turned-no-go stimuli, the time delay between appearing on the screen and turning into the star is fully random and not tied to participant performance.

A subset of participants (n = 75) will complete all 10 levels of the mobile application a second time approximately 1 week after their first time playing. These data will be used to assess the stability of mobile application-derived behavioral measures.

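### The plan credits the ICC with capturing agreement but fixes the consistency form, so a uniform practice gain between the two plays would show in neither planned stability statistic

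*Protocol article*

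**What the plan says.** Under Participants, the article gives the size of the retest subset: "we will invite 75 youth out of the overall sample of 200 to play CALM-IT twice". Under CALM-IT mobile application, it says that these children "will complete all 10 levels of the mobile application a second time approximately 1 week after their first time playing".

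The analysis is set out under Stability of mobile application-based behaviors, in the Analytic plan for Aim 1. The first statistic is "examination of correlation between time-one with time-two measures of percentage of targets hit, percentage of stars hit, and d"-prime. The second is an ICC, with this reason for adding it: "In contrast to the Pearson’s correlation coefficient, ICC captures not only the degree of correlation, but also the agreement across measurements". The form is then fixed: "we will use ICC(3,1) which is a two-way mixed effects assessment of consistency within a single measurement". Verbal bands follow with cut-points at 0.40, 0.70 and 0.90, for example "an ICC value of 0.70–0.90 would indicate good consistency".

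The Introduction describes the later use of the app as one that "would allow clinicians and researchers to screen for and track inhibitory control deficits in the community".

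**The concern.** What the ICC can add to a correlation, on the article's own reasoning, is agreement: whether a child gets the same score twice, and not only the same place in the group. There are two usual single-measure two-way forms. The absolute-agreement form counts a shift in the session mean as disagreement. The consistency form removes that shift before the coefficient is computed. The article gives the reason for the first and names the second.

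This matters because the second play repeats the same ten levels about a week later, with a running score and error feedback in the game, so a practice gain is plausible. The correlation cannot see a common shift either. The engagement section reports average hit percentages over participants and by level, but does not compare the first play with the second. As written, Aim 1b could therefore report good stability for a score whose level has moved. If the app is later used to track a child, a gain from replay alone could be read as improvement.

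**Working it through.** **Inputs from the article.** Two sessions; 75 children invited to the retest; ICC(3,1), consistency, single measurement; bands at 0.40, 0.70 and 0.90; significance level 0.05 and power 0.80, with a detectable r of 0.32 for Aim 1b.

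**Assumed inputs.** The article gives no expected ICC and no practice gain. I take a consistency ICC (rho) of 0.80 or 0.75, equal session variances (SD 1), and a uniform shift of d SD. The shift enters squared, so its direction does not matter.

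**The plan's own figure.** With a two-sided test (sidedness is not stated), the Fisher z approximation gives tanh((1.960 + 0.842)/√72) = 0.319. The method of the pwr package gives 0.317, with power 0.808 at r = 0.32. The stated 0.32 reproduces and is not affected by this point.

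**What ICC(3,1) contains.** With MSR the mean square between children, MSE the residual and MSC the session mean square, for two sessions:

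- MSR = (var1 + var2)/2 + cov and MSE = (var1 + var2)/2 − cov.
- ICC(3,1) = (MSR − MSE)/(MSR + MSE) = 2·cov/(var1 + var2).

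MSC does not appear. With equal variances the expression equals Pearson's r.

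**What absolute agreement contains.** ICC(2,1) = (MSR − MSE)/(MSR + MSE + 2(MSC − MSE)/n). Two sessions that differ by d have a session variance of d²/2, so the population value is rho/(1 + d²/2).

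| Uniform shift d (SD) | 1 + d²/2 | Agreement ICC when ICC(3,1) = 0.80 | Agreement ICC when ICC(3,1) = 0.75 |
|---|---|---|---|
| 0 | 1.000 | 0.80 | 0.75 |
| 0.3 | 1.045 | 0.77 | 0.72 |
| 0.5 | 1.125 | 0.71 | 0.67 |
| 0.8 | 1.320 | 0.61 | 0.57 |
| 1.0 | 1.500 | 0.53 | 0.50 |

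ICC(3,1) stays at 0.80 or 0.75 in every row. On constructed data sets of 75 pairs, adding constants of up to 5 SD to session 2 left r and ICC(3,1) unchanged to four decimals. At rho 0.80, ICC(2,1) fell from 0.80 to 0.06.

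**Where the band changes.** Setting rho/(1 + d²/2) = 0.70 gives d = √(2(rho/0.70 − 1)). For rho = 0.80, d = √0.2857 = 0.53. For rho = 0.75, d = √0.1429 = 0.38.

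**When the gain is not uniform** (assumed illustrations, starting from about 0.80):

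- Gains that vary between children with SD 0.6: 2(0.80)/(1 + 1.36) = 0.68.
- Session-2 spread halved: 2(0.80)(0.5)/(1 + 0.25) = 0.64, while r stays at 0.80.
- A 10-point gain on a percentage with mean 85, SD 8 and a cap of 100, by simulation: 0.74.

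Here ICC(3,1) does fall, because spread or rank order has changed and not because the mean has moved.

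**The case against.** The strongest reply is that consistency is what the article means to measure. The Aim 1 heading uses that word, the ICC is introduced as a measure of it, and every band is labelled with it. Only one general sentence speaks of agreement. Within this study d-prime is used to compare children, in the regression on the laboratory factor (Aim 2) and on symptoms (Aim 3), and relative consistency is a suitable reliability for that. Tracking is a later hope: the article sets no cut-off and analyses no individual change, and screening could rest on a first play. The ICC drives no test, sample size or go/no-go rule. A condensed article may also leave session means and confidence intervals to a fuller plan.

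Most of this stands, and it limits the severity. It does not remove the point, which concerns what the article states: it gives agreement as the reason and names a form that excludes it.

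A reader might infer that a practice effect of any size would leave the rating untouched. The documents do not support that. It is true only of a uniform additive gain; targets hit and stars hit are bounded percentages, and uneven or capped gains lower ICC(3,1). Nor does ICC(3,1) merely repeat r in all cases, since it falls below r when the session variances differ.

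**Conclusion.** The point holds as an inconsistency between rationale and statistic, with a real gap behind it. The article's two stability statistics cannot register a uniform change in level, and it plans no comparison of session means. The size depends on values that the article does not give. With equal variances and a consistency of 0.80, gains of 0.3 and 0.5 SD would still be rated good on absolute agreement. The rating would become moderate only above about 0.53 SD, or about 0.38 SD from a starting value of 0.75. The documents do not show that such a gain will occur.

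A reader might also conclude that Aim 1b fails without this change. It does not: reliability of relative standing is validly assessed, and Aims 2 and 3 can rely on it. Severity is moderate.

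**What to change.** - Report the two-way absolute-agreement single-measure ICC with its 95% CI, beside ICC(3,1).
- Report the mean change from session 1 to session 2 for targets hit, stars hit and d-prime.
- Base any statement about agreement or stability of level on these two results.
- Keep ICC(3,1) and its consistency bands for rank-order reliability.
- Reword the sentence that attributes agreement to the ICC, so that it describes the absolute-agreement form only.

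Deleting the agreement rationale alone would remove the contradiction, but it would leave a shift in level unexamined.

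The cost is a few lines of text and one software option. The same pairs of scores suffice, with no change to sample size or conduct. The downside is that the agreement reported may be lower if there is a practice effect.
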